#### Secondary Outcomes

Composite adverse perinatal outcome will be defined as the presence of at least one of the following: fetal death, Apgar score <7 at 5 minutes, UA pH <7.05, admission to the NICU or a transitional care unit within 48 hours, birthweight <2000 grams, maternal admission to the obstetric intensive care unit within 48 hours (before or after delivery), and PE.

Composite adverse neonatal outcomes will be defined as the presence of at least one of the following: respiratory distress syndrome (respiratory rate >60 or <30 breaths/min, grunting on expiration, chest indrawing, central cyanosis, apnea, or the need for surfactant therapy in the neonatal period) [62], transient tachypnea, required ventilatory support, grade III or IV intraventricular hemorrhage, neonatal sepsis, hypoglycemia, necrotizing enterocolitis, neonatal jaundice (treated with phototherapy), neonatal seizures, pneumonia, meningitis, and neonatal death.

Other secondary outcomes will include the following: rates of elective delivery before 38, 39, and 40 weeks of gestation; rates of deliveries (elective and spontaneous) before 38, 39, and 40 weeks of gestation; rate of birthweight <2500 grams; rate of UA pH <7.10; rate of elective cesarean delivery; rate of cesarean delivery due to failed labor induction; rate of emergency operative vaginal delivery; and rate of placental-related complications, such as placental abruption, pregnancy hypertension, severe PE, eclampsia, stroke, maternal death, and postpartum hemorrhage.

### Statistical Analysis

Statistical analysis will be performed based on the intention-to-treat approach, considering all randomized women. A sensitivity analysis will be carried out to take into account the effect of withdrawal of consent and loss to follow-up. Outcomes and covariates will be imputed by multiple imputation chain equations. Patients deemed ineligible after randomization (eg, due to identification of congenital defects or EFW >10th percentile) will be excluded in the per-protocol analysis.

Univariate descriptive analysis will be used for the study variables. We will assess differences between the groups for the primary and secondary outcomes, calculating differences in the incidence and relative risks with their respective 95% CIs. Type I errors will be set at *P*<.05. The statistical software packages R and R Studio (R Foundation) will be used for statistical analyses. An interim analysis will be performed by an independent statistician once 50% of the sample size has been recruited. This analysis will ascertain the safety of the new approach with the O’Brien-Fleming boundary [63]. As FGR pregnancies have a higher risk of stillbirth and other adverse outcomes compared to SGA pregnancies, women with SGA fetuses will probably be more willing to participate. Enrollment of a greater proportion of SGA pregnancies might hinder identification of differences between groups. For this reason, a subgroup analysis will be performed for FGR and SGA pregnancies according to the Doppler classification at enrollment. Categorical variables will be reported as frequencies, normally distributed continuous variables will be reported as means and standard deviations, and continuous variables that do not follow a normal distribution will be reported as medians and interquartile ranges. The Fisher exact test or chi-square test, as appropriate, will be used to assess differences in categorical variables between groups. The Student *t* test (2-tailed) or Mann-Whitney *U* test, as appropriate, will be used for continuous variables.

During the design stage of the trial, no financial support was available. Nevertheless, if this trial receives a specific grant from a funding agency, monitoring by the Academic Research Organization of the Vall d’Hebron Research Institute will be contracted.

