### Trial Design

This is a multicenter, open-label, randomized clinical trial. The study design adheres to the SPIRIT (Standard Protocol Items: Recommendations for Interventional Trials) quality standard criteria for randomized trials [43]. A pragmatic approach will be adopted in order to evaluate the effectiveness of the intervention in real-life, routine practice conditions. Therefore, each participating site will use the fetal growth charts, Doppler reference values, and methods for cervical ripening and labor induction usually applied in their clinical practice.

The clinical trial was entered in the ClinicalTrials.org registry on August 6, 2020 (NCT04502823).

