### Intervention

First, gestational age (by fetal crown-rump length measurement at 11+0 to 13+6 weeks+days) [44] and EFW ≤10th percentile will be confirmed [45-49]. After giving their written informed consent, trial participants will be randomized into 2 groups: intervention and control.

In the intervention group, the sFlt-1/PlGF ratio will be revealed to investigators so they can act according to the results. When the sFlt-1/PlGF ratio is ≥38, the fetus will be classified as FGR. The remaining cases will be classified as SGA. In the intervention group, the UA PI, MCA PI, CPR, and UtA PI percentiles will be concealed to obstetricians in order to avoid any influence that this information might have on their interpretation of fetal movements or CTG.

In the control group, the sFlt-1/PlGF ratio will be concealed to investigators and the standard Doppler-based approach will be used for fetal monitoring [1]. Thus, fetuses with an EFW <3rd percentile or ≤10th percentile accompanied by an abnormal feto-maternal Doppler (UA PI >95th percentile, MCA PI <5th percentile, CPR <5th percentile, UtA PI >95th percentile, or a combination of these markers) [50-53] will be classified as FGR. The remaining cases will be classified as SGA.

In both groups, when a fetus is classified as FGR, immediate (within 24 hours) elective delivery at ≥37 weeks of gestation will be recommended; when a fetus is classified as SGA, elective delivery will be delayed until 40 weeks of gestation. From randomization to delivery, all SGA pregnancies in both groups will receive weekly follow-ups consisting of fetal ultrasound (including fetal growth, amniotic fluid deepest vertical pocket, fetal movements, and feto-maternal Doppler), conventional CTG, and measurement of the sFlt-1/PlGF ratio (which will be concealed or revealed depending on the allocated group).

In both groups, if at any time after enrollment any of the following is present, immediate (within 24 hours) delivery will be recommended: UA with absent or reversed end-diastolic flow, nonreassuring CTG, PE, diminished fetal movements, biophysical profile score ≤6, or oligohydramnios (largest vertical pocket <2 cm). The flow chart in Figure 1 illustrates the management of participants from consent through follow-up.

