### Sample Size

A management protocol based on EFW and Doppler assessment has shown a prevalence of adverse perinatal outcomes of 26%, meaning that there is a prevalence of 74% of pregnancies with no complications [25]. The estimated rate of pregnancies with no complications in the intervention group has been set at 74%, with a lower limit of 65.5% (a maximum achievable difference of 8.5%). Based on these considerations and an estimated dropout rate of 3%, the sample size needed for a noninferiority design with a power of 80% and a significance level of 5% is 1030 participants, that is, 515 in each group. Noninferiority will be demonstrated if the lower limit of the 95% CI of the difference between incidences of pregnancies without neonatal acidosis is less than –8.5%. If the dropout rate is greater than 3%, the number of participants will be increased so as to achieve 1000 participants with complete data for the primary outcome.

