### Randomization, Masking, and Data Collection

Participants will be randomly assigned to the intervention or control group in a 1:1 ratio using variable-size block randomization. The randomization sequence will be centralized and generated by the web-based system Sealed Envelope (Sealed Envelope Ltd) and will be concealed to investigators. Owing to the nature of the intervention, it will not be possible to conceal the study group to the participants, investigators, or outcome assessors.

A RedCap (Research Electronic Data Capture; Vanderbilt University) electronic database has been specifically designed for this study [64]. The electronic database has a randomization module that will allow allocation of participants to the study groups. Data will be entered prospectively during the study. Access to this database will be restricted to the investigators involved in each participating site.

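### The per-protocol set, as written, screens only for eligibility, so it gives little check on dilution of the intention-to-treat noninferiority contrast by management against allocation

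*Protocol article*

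**What the plan says.** The Statistical Analysis section of the protocol article sets the main approach: "Statistical analysis will be performed based on the intention-to-treat approach, considering all randomized women". It then gives the only stated rule for a second set: "Patients deemed ineligible after randomization (eg, due to identification of congenital defects or EFW >10th percentile) will be excluded in the per-protocol analysis". The bracketed examples illustrate ineligibility and are not further grounds for exclusion. One other robustness analysis is planned: "A sensitivity analysis will be carried out to take into account the effect of withdrawal of consent and loss to follow-up". Management against the allocated classification is not mentioned.

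The Sample Size section sets the margin at 8.5 percentage points, judged on the lower limit of a 95% confidence interval. It does not say which analysis set the rule applies to and gives the per-protocol result no role.

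On conduct, the Intervention section says that for a fetus classified as FGR "immediate (within 24 hours) elective delivery at ≥37 weeks of gestation will be recommended"; for SGA, elective delivery is deferred to 40 weeks. The Randomization, Masking, and Data Collection section adds that "it will not be possible to conceal the study group to the participants, investigators, or outcome assessors". The Trial Design section states the aim: "A pragmatic approach will be adopted in order to evaluate the effectiveness of the intervention in real-life, routine practice conditions".

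**The concern.** In a superiority trial, departures from allocated management usually pull the intention-to-treat estimate toward zero and count against the claim. In a noninferiority trial the same pull counts in favor of it. A per-protocol set is normally reported beside intention-to-treat because it responds differently to such departures. A set that removes only ineligible women does not do this: a woman labelled SGA but delivered early, or labelled FGR who declines early delivery, remains in both sets.

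Departures are plausible on the article's own terms:

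- Delivery timing is a recommendation, and everyone knows the allocation.
- In the intervention arm the Doppler percentiles are concealed from obstetricians, but the estimated fetal weight percentile is not among the concealed items. A weight below the 3rd percentile is enough for FGR under the control-arm rule.
- The note to Table 1 says that the classification used for labor induction follows the Doppler criteria, as in the control group. Six of the 20 sites list different ripening methods for FGR and SGA, so the Doppler class may be needed there. This sits uneasily with the concealment.

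At stake is whether a noninferiority finding reflects the classification or reflects arms that were managed more alike than planned.

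**Working it through.** **Inputs.** Rate without complications 74% in both arms (Sample Size: "meaning that there is a prevalence of 74% of pregnancies with no complications"); margin 8.5 points; 95% confidence interval, so one-sided 2.5%; 1000 women with complete data, 500 per arm. I read the rule as requiring the lower limit to lie above –8.5 points on the 74% scale.

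**The plan's own figure.** The usual noninferiority formula gives n = 2 × 0.74 × 0.26 × (1.96 + 0.842)² / 0.085² ≈ 419 per arm. That is 838 in total, and 838 / 0.97 ≈ 864 after 3% dropout. The stated 1030 is not reproduced; it is larger than its inputs require. This does not affect the present point, and I use the planned 500 per arm.

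**Power at the planned size.** SE = √(2 × 0.74 × 0.26 / 500) = 0.0277. Power = Φ(0.085 / 0.0277 – 1.96) ≈ 86.5%.

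**Dilution.** Let c be the share of the between-arm contrast lost to management against allocation. The intention-to-treat difference is then d = –0.085 × (1 – c) when the difference under full adherence equals the margin. With p = 0.74 + d in the intervention arm, SE = √{[0.74 × 0.26 + p(1 – p)] / 500}, and the probability of declaring noninferiority is Φ((d + 0.085) / SE – 1.96).

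| c | d (points) | SE | Probability |
|---|---|---|---|
| 0 | –8.50 | 0.0289 | 2.5% |
| 10% | –7.65 | 0.0288 | 4.8% |
| 20% | –6.80 | 0.0287 | 8.6% |
| 30% | –5.95 | 0.0286 | 14.3% |

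If a fraction f of each arm receives the other arm's management, c = 2f. Thus 10% crossing in each arm is the 20% row. With a true difference of –10 points, the corresponding probabilities are 0.7%, 1.7%, 3.7% and 7.5%.

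**Women whose management the trial can change.** In the observational study described under Management of SGA: Angiogenic Factors, 412 of 521 small fetuses were FGR by Doppler and 102 of 521 by the ratio. These are marginal counts, and the cross-table is not given. The discordant share is smallest if every high-ratio fetus is also Doppler-FGR: (412 – 102) / 521 = 59.5%. It is largest if none is: (412 + 102) / 521 = 98.7%. If concordant women are unaffected, an overall loss of 8.5 points corresponds to between 8.5 / 0.987 = 8.6 and 8.5 / 0.595 = 14.3 points in discordant women.

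**Cost of a stricter per-protocol set.** If 10% are excluded, 450 per arm remain: SE = √(2 × 0.74 × 0.26 / 450) = 0.0292, and power = Φ(2.907 – 1.96) ≈ 83%.

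**The case against.** The strongest reply is that the article never says that ineligibility is the sole exclusion. It is a condensed account of a fuller protocol, and a complete per-protocol definition may sit there or in an analysis plan that is not shown. This stands in part: one should not infer that the trial has no adherence criterion anywhere. But the article did choose to state an exclusion rule, and the rule it states omits adherence.

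Four stronger readings are tempting and are not supported:

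- **That nothing in the plan would reveal poor adherence.** Rates of elective and of all deliveries before 38, 39 and 40 weeks are planned secondary outcomes and would show gross convergence between arms. They would not correct the primary contrast.
- **That women given the same plan under both classifications are a further source of bias.** The trial compares two strategies in all small fetuses, and these women belong to that comparison.
- **That 59.5% is the proportion reclassified.** It is a net difference and therefore a minimum, so 14.3 points is a ceiling and not an estimate.
- **That false noninferiority will in fact be inflated by a stated amount.** No adherence rate is given. Concealing Doppler percentiles in one arm and the ratio in the other limits deliberate crossover.

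The pragmatic aim also carries weight. If the question is how the strategies perform with whatever adherence routine care brings, intention-to-treat is the right primary contrast, and a diluted difference is part of the answer. Excluding women by how they were managed conditions on events after randomization that may be related to prognosis. Making the claim depend equally on both sets is therefore one convention and not the correction of an error. The planned subgroup analysis by Doppler class at enrollment also partly covers the comparison in discordant women, because its FGR stratum contains every woman whom the ratio moves from FGR to SGA.

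**Conclusion.** The point holds in a limited form. As the article words it, the per-protocol set is an eligibility set, nearly repeats intention-to-treat, and offers little check on a dilution that favors noninferiority. The direction is certain only to the extent that departures resemble the other arm's management in women whom the two classifications label differently. The size is conditional: at a true difference equal to the margin, the 2.5% error becomes about 4.8%, 8.6% or 14.3% if 10%, 20% or 30% of the contrast is lost. These errors are relative to the effect under full adherence, and the losses are assumed. This does not invalidate the primary analysis. It is a weakness in the supporting analyses that should be repaired before the data are examined.

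**What to change.** 1. Keep intention-to-treat as the primary analysis and name it in the noninferiority rule.
2. Define the per-protocol set as eligible women managed in line with their allocated classification. Count delivery after any of the triggers for immediate delivery listed in the Intervention section as adherent. If the full protocol or analysis plan already says this, one sentence in the article is enough.
3. Report the per-protocol confidence limit against the same –8.5-point margin as a required supportive analysis, and state in advance that disagreement with intention-to-treat qualifies the noninferiority claim.
4. Add, as a supportive analysis, the same contrast in women whose baseline Doppler and sFlt-1/PlGF classifications disagree. The ratio is an inclusion criterion and Doppler class at enrollment is already used for a subgroup, so the data should exist. The comparison remains randomized provided both classifications are fixed before allocation.
5. Reconcile the Table 1 note on Doppler-based classification for induction with the concealment of Doppler percentiles in the intervention arm.

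The cost is wording and analysis time. The per-protocol set loses some precision (about 83% power if 10% are excluded, against 86.5%) and may carry selection bias, which is why it should support the primary analysis and not replace it.

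### The primary comparison is crude although EFW, Doppler class and sFlt-1/PlGF ratio are known at enrollment; a prespecified adjusted risk difference would be a modest efficiency gain, not a correction

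*Protocol article*

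**What the plan says.** Under Statistical Analysis, differences between groups for primary and secondary outcomes are assessed by "calculating differences in the incidence and relative risks with their respective 95% CIs". The same section adds that "The Fisher exact test or chi-square test, as appropriate, will be used to assess differences in categorical variables between groups". No regression model, adjustment covariate or site term is named. Covariates are mentioned once, as something to be imputed: "Outcomes and covariates will be imputed by multiple imputation chain equations".

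Baseline prognosis enters in one place only: "a subgroup analysis will be performed for FGR and SGA pregnancies according to the Doppler classification at enrollment". Under Randomization, Masking, and Data Collection, allocation is "in a 1:1 ratio using variable-size block randomization", with no stratification factor given. Under Trial Design, "each participating site will use the fetal growth charts, Doppler reference values, and methods for cervical ripening and labor induction usually applied" in that site's practice. Tables 1 and 2 show the resulting spread over 20 hospitals.

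The Inclusion Criteria require an EFW and an sFlt-1/PlGF ratio at 36+0 to 37+6 weeks. The Intervention section conceals Doppler percentiles from obstetricians in the intervention arm, but the planned subgroup analysis requires them to be recorded there too.

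**The concern.** The article regards these baseline variables as prognostic. The Introduction describes adverse outcome as rising when EFW falls, when Doppler is abnormal and when the ratio is higher. Statistical Analysis repeats that growth-restricted pregnancies carry more risk than small-for-gestational-age ones. As written, though, neither the allocation nor the primary estimate uses that information.

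In a noninferiority trial the decision depends on how far the confidence limit lies from the margin. Explaining part of the outcome variance with values fixed before treatment shortens the interval without recruiting anyone. It also takes account of any chance difference between arms in the modelled factors. What is at stake is some precision and a little robustness. Validity is not at stake.

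**Working it through.** **Inputs from Sample Size.** Adverse outcome 26% in both arms (74% without complications), margin 8.5 points, stated power 80%, 3% dropout, 1030 randomized, 1000 women with complete data. Decisions rest on a 95% CI limit, which I take as one-sided 2.5%. The wording of that decision rule is a separate matter. I use only the fact that a confidence limit for a difference is set against 8.5 points.

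**The plan's own figure.** The usual noninferiority formula gives (1.96 + 0.8416)² × 2 × 0.26 × 0.74 / 0.085² = 7.849 × 0.3848 / 0.007225 ≈ 418.03, so 419 per arm. Then 419/0.97 gives 432 per arm, or 864 in all. This does not reproduce 1030. It is a separate question. Here it means only that the trial is larger than its stated inputs require by this formula, so I start from 500 complete women per arm.

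**Crude analysis.** SE = √(0.3848/500) = 2.77 points. The 95% half-width is 1.96 × 2.77 = 5.44 points. Power = Φ(8.5/2.774 − 1.96) = Φ(1.104) = 86.5%.

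**Adjusted analysis.** If covariates explain a share R² of outcome variance, the variance is multiplied by about (1 − R²). Power becomes Φ(3.064/√(1 − R²) − 1.96), and the equivalent number of complete women is 1000/(1 − R²).

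| Assumed R² | Half-width (points) | Power | Equivalent women |
|---|---|---|---|
| 0 | 5.44 | 86.5% | 1000 |
| 0.05 | 5.30 | 88.2% | 1053 |
| 0.10 | 5.16 | 89.8% | 1111 |

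**Which R² is plausible?** The documents do not say. The only figures are negative predictive values of about 99% in an earlier observational study, and they cannot be carried over. There, 521 − 102 = 419 women were below the ratio cut-off, with about 4 events at 1%. Even if all 102 others had events, the rate would be 106/521 = 20.3%, below the 26% assumed here, so a different outcome was being predicted.

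For a binary factor with prevalence q, R² = q(1 − q)(r₁ − r₀)²/[p(1 − p)]. The risks below are assumptions:
- q = 60%, risks 32.5% and 16.25%: R² = 0.03.
- q = 60%, risks 35% and 12% (overall 25.8%): R² = 0.066.
- The same risks at the article's other share, q = 79.1% (overall 30.2%): R² = 0.041.
- q = 19.6% (share with ratio ≥38), risk ratio 3: R² = 0.11.
- Site risks with an SD of 5 points: 0.05²/0.1924 = 0.013.

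**Simulation checks (ratio of adjusted to crude variance).**
- Doppler class alone, 6,000 trials per scenario: 1.00 with no association, 0.97 at R² 0.033, 0.93 at R² 0.066.
- Three baseline factors plus 20 site indicators, 600 trials per scenario: 1.01 at R² 0, 1.05 at 0.03, 0.96 at 0.06, 0.84 at 0.135.

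One factor costs nothing measurable if it is useless. Twenty site terms can cancel the gain when predictors are weak.

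**Chance imbalance.** The SD of the between-arm difference in a 60% factor is √(2 × 0.6 × 0.4/500) = 3.1 points. If that factor moves risk by an assumed 15 points, the crude difference shifts by about 0.5 point (1 SD). With 23 points and a 2-SD imbalance the shift is 6.2 × 0.23 = 1.4 points. That is 17% of the margin, but well inside the half-width of 5.44.

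**The case against.** The strongest reply is that nothing here is wrong. Under 1:1 randomization the crude difference is unbiased and its interval already allows for chance imbalance. With no stratification stated, adjustment is not needed for error control. Power is already above the 80% target. A covariate list and stratification factors often sit in an analysis plan or full protocol, neither of which is shown, and the sentence on imputing covariates hints at some planned role for them. All of this stands. It makes the point a recommendation. It does not remove it, because the article does state its method for the primary comparison, and that method is crude.

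A reader might also infer that the Fisher and chi-square tests are meant to decide noninferiority, which a test of equality cannot do. The documents do not support that. The sentence concerns categorical variables in general, and Sample Size rests the decision on a confidence limit for the difference.

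One technical objection also stands: Mantel-Haenszel stratification is not a substitute for the model, because it cannot take a continuous log ratio, and strata of site by class by EFW would be sparse.

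**Conclusion.** The primary comparison as stated is unadjusted, while three baseline variables that the article treats as prognostic are available in every woman. Using them would be an efficiency improvement. The size depends on an R² that the documents do not give: over 0 to 0.10, power goes from 86.5% to about 90% and the half-width from 5.44 to 5.16 points. These figures assume 26% risk in both arms, 500 complete women per arm and one-sided 2.5%, and ignore the interim analysis.

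Three stronger readings are tempting and do not hold:
- That the crude result would be biased or its noninferiority verdict unsound. Randomization protects it.
- That the predictors are strong and the precision free. No passage quantifies prediction of this outcome, and a model with many site terms may gain nothing.
- That adjustment removes chance imbalance. It deals only with the modelled factors, and the imbalance to be expected at this size is small.

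**What to change.** Before any comparison by arm, prespecify the primary estimate as a standardized (marginal) risk difference with 95% CI from a logistic model containing treatment and three covariates: Doppler class at enrollment, EFW below the 3rd versus 3rd to 10th percentile, and log sFlt-1/PlGF ratio.

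- Use enrollment values only. Doppler and the ratio are repeated weekly in follow-up, and later values are post-randomization.
- The Doppler-based class already counts every EFW below the 3rd percentile as growth restricted, so the first two covariates define three levels, not four. Say so in the specification.
- Include site parsimoniously, for example grouped by chart set in Table 2 or with a stated pooling rule, and not as 20 separate terms.
- Judge noninferiority on this interval against the 8.5-point margin, which keeps its meaning because the estimate stays on the absolute scale. Report the crude difference as a sensitivity analysis.

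If an existing analysis plan already specifies this, the sponsor need only confirm it. Otherwise the cost is a paragraph of wording, slightly more analysis work, and a negligible loss of precision should the short covariate list turn out not to be prognostic. Fixing the list in advance also prevents covariates from being chosen after the results are seen, which matters in an open-label trial.
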